## Abstract

****Background**:**

Multi-element interventions for first-episode psychosis (FEP) are promising, but have mostly been conducted in non-epidemiologically representative samples, thereby raising the risk of underestimating the complexities involved in treating FEP in ‘real-world’ services.

****Methods/Design**:**

The Psychosis early Intervention and Assessment of Needs and Outcome (PIANO) trial is part of a larger research program (Genetics, Endophenotypes and Treatment: Understanding early Psychosis - GET UP) which aims to compare, at 9 months, the effectiveness of a multi-component psychosocial intervention versus treatment as usual (TAU) in a large epidemiologically based cohort of patients with FEP and their family members recruited from all public community mental health centers (CMHCs) located in two entire regions of Italy (Veneto and Emilia Romagna), and in the cities of Florence, Milan and Bolzano. The GET UP PIANO trial has a pragmatic cluster randomized controlled design. The randomized units (clusters) are the CMHCs, and the units of observation are the centers’ patients and their family members. Patients in the experimental group will receive TAU plus: 1) cognitive behavioral therapy sessions, 2) psycho-educational sessions for family members, and 3) case management. Patient enrolment will take place over a 1-year period. Several psychopathological, psychological, functioning, and service use variables will be assessed at baseline and follow-up. The primary outcomes are: 1) change from baseline to follow-up in positive and negative symptoms’ severity and subjective appraisal; 2) relapse occurrences between baseline and follow-up, that is, episodes resulting in admission and/or any case-note records of re-emergence of positive psychotic symptoms. The expected number of recruited patients is about 400, and that of relatives about 300. Owing to the implementation of the intervention at the CMHC level, the blinding of patients, clinicians, and raters is not possible, but every effort will be made to preserve the independency of the raters. We expect that this study will generate evidence on the best treatments for FEP, and will identify barriers that may hinder its feasibility in ‘real-world’ clinical settings, patient/family conditions that may render this intervention ineffective or inappropriate, and clinical, psychological, environmental, and service organization predictors of treatment effectiveness, compliance, and service satisfaction.

****Trial registration**:**

ClinicalTrials.gov Identifier NCT01436331

## **Background**

It has been suggested that most clinical and psychosocial deterioration in psychosis occurs within the first 5 years of illness onset, and that this timeframe is a crucial period for initiating treatment [1]. Recent research efforts have therefore focused on early detection and intervention for psychosis, showing that the beneficial effects of antipsychotic medication on first-episode psychosis (FEP) are tempered by the fact that, despite initial symptom reduction, functional recovery is typically poor even when optimal pharmacological treatment is provided [2]. Family members are also affected by the emotional burden of being caregivers, and often show signs of psychological distress themselves [3]. It is clear from the literature that pharmacotherapy alone is not sufficient to prevent relapses or assure functional recovery from acute psychosis [4].

Over the past few years, there has been a growing interest in psychosocial intervention as a means of facilitating recovery and reducing long-term disability associated with psychosis [5]. Literature on psychosocial interventions in FEP can be viewed in terms of two broad categories [6]: 1) studies evaluating specific (that is, single-element) psychosocial interventions (for example, individual cognitive behavioral therapy), and 2) studies evaluating comprehensive (that is, multi-element) interventions, which may include: early detection strategies; individual, group, and/or family therapy; and case management (in addition to pharmacological treatment). These interventions appear promising [7] and have been found to be associated with symptom reduction/remission, improved quality of life, increased social and cognitive functioning, low inpatient admission rates, improved insight, high degree of satisfaction with treatment, less time spent in hospital, decreased substance abuse, and fewer self-harm episodes.

However, most multi-element research programs have been conducted in non-epidemiologically representative samples in experimental settings, thereby raising the risk of underestimating the complexities involved in treating FEP in ‘real-world’ services [8]. Moreover, these interventions have rarely been tested for their efficacy against a control group, but more typically against historical or prospective comparison groups, and usually only single-group studies have been carried out, which track the progress of a single group over a given period.

With respect to clinical practice, some countries have implemented specific early psychosis interventions over the past 10 years, but even these have not yet become routine [9]. Few studies have identified barriers that may hinder the feasibility of these interventions or the patient or family conditions that may render this type of treatment ineffective or inappropriate. Hence, efforts to implement multi-element interventions targeted to FEP in routine services should be accompanied by rigorous scientific method, with the aim of better understanding the actual effectiveness of this approach [10,11].

## **Methods/Design**

### **Aims**

The Psychosis early Intervention and Assessment of Needs and Outcome (PIANO) trial is part of the larger research program termed Genetics Endophenotypes and Treatment: Understanding early Psychosis (GET UP; national coordinator: [name], Verona), funded by the Italian Ministry of Health as part of a National Health Care Research Program (Ricerca Sanitaria Finalizzata) coordinated by the Academic Hospital of Verona (Azienda Ospedaliera Universitaria Integrata Verona).

GET UP consists of four partner projects : PIANO, TRaining and Understanding of service Models for Psychosis Early Treatment (TRUMPET), Genetic data Utilization and Implementation of Targeted drug Administration in the clinical Routine (GUITAR) and COgnitive Neuroendophenotypes for Treatment and RehAbilitation of psychoses: Brain imaging, InflAmmation and StresS (CONTRABASS). Each of these partner projects pertains to different areas of research, but they are linked together.

The GET UP PIANO trial described here is the main data collection axis for the overall GET UP Research Program. The trial has three aims:

1) To compare, at 9 months, the effectiveness of a multi-component psychosocial intervention with that of treatment as usual (TAU) in a large epidemiologically based cohort of patients with FEP and their family members recruited from a 10 million-inhabitant catchment area.

2) To identify the barriers that may hinder its feasibility in real-world routine clinical settings and patient/family conditions that may render this intervention ineffective or inappropriate.

3) To identify clinical, psychological, environmental, and service organization predictors of treatment effectiveness, compliance, and service satisfaction in FEP in the Italian community mental healthcare framework.

Study participants are recruited from community mental health centers (CMHCs) operating for the Italian National Health Service and located in two entire regions of Italy (Veneto and Emilia Romagna), and in the cities of Florence, Milan and Bolzano. For administrative and research purposes, the overall territory covered by the GET UP has been divided into eight macro-areas, named participating units (PUs): Western Veneto, Eastern Veneto, Emilia, Romagna, Florence, Bolzano, Milan Niguarda, and Milan San Paolo.

### **Design**

The PIANO trial has a pragmatic cluster randomized controlled design [12,13], which compares the effectiveness of TAU plus a multi-element psychosocial treatment for patients with FEP and their family members, versus TAU alone, as provided by Italian community mental health services. A cluster design was chosen based on feasibility considerations, supported by the MRC Health Services and Public Health Research Board [14], which indicated that cluster randomization is the gold standard approach for trials evaluating similar complex interventions implemented at the institutional level, with the aim of improving health. The assignment units (clusters) are the CMHCs located in the catchment area, and the units of observation and analysis are the CMHC patients and their family members. Each CMHC belongs to the Department of Mental Health (DMH), which is responsible for all mental health care (including outpatient, inpatient, and long-term residential care) for a specific catchment area. Each DMH can include one or several CMHCs, depending on the size of the DMH catchment area.

### **Inclusion and exclusion criteria**

Inclusion criteria are based on the screening method adopted in the WHO 10-country study [15], and include:

· Age 18–54 years.

· Residence in the catchment area of participating CMHCs.

· Presence of 1) at least one of the following symptoms: hallucinations, delusions, qualitative speech disorder, qualitative psychomotor disorder, bizarre or grossly inappropriate behavior; or 2) at least two of the following symptoms: loss of interest, initiative and drive, social withdrawal, episodic severe excitement, purposeless destructiveness, overwhelming fear, marked self-neglect, as measured by the Screening Schedule for Psychosis [15].

· First lifetime contact with participating CMHCs, prompted by the symptoms enumerated in the point above.

Exclusion criteria are:

· Pre-existing anti-psychotic medication (> 3 months) prescribed by any psychiatric or other medical agencies for a mental disorder identical or similar to the current one.

· Mental disorders due to a general medical condition.

· Moderate to severe mental retardation as determined by clinical functional assessment.

· An ICD-10 diagnosis other than F20-F29, F30.2, F31.2, F31.5, F31.6, F32.3, F33.3, F1x.4; F1x.5, F1x.7, F1x.8, F1x.9, as confirmed after 9 months by using the Schedule for Clinical Assessment in Neuropsychiatry (SCAN) [16].

### **Ethical issues**

This study is being conducted in accordance with globally accepted standards of good clinical practice, in agreement with the Declaration of Helsinki, and in keeping with local regulations.

GET UP PIANO investigators ensure that all professionals involved in the trial are adequately qualified and informed about the protocol, the study interventions, and their trial-related duties and functions. The coordinating center maintains a list of all appropriately qualified persons involved in the study.

#### ***Ethics committee approval***

Formal ethics approval for conducting the trial has been sought and obtained by the Coordinating Center’s Ethics Committee (Comitato Etico per la Sperimentazione, Azienda Ospedaliera di Verona, http://www.ospedaliverona.it/Istituzionale/Comitati-Etici/Sperimentazione), which approved the study protocol, the information sheets (patient and family versions), and the informed consent sheets (patient and familiar versions) on 6 May 2009 (Prot. N. 20406/CE, Date 14/05/2009), and by the ethics committee of each participating unit.

### **Interventions**

#### ***Experimental treatment***

The experimental treatment package is provided by routine public CMHCs, which operate within the Italian National Health Service and consists of TAU (see next paragraph) plus evidence-based additional treatment. Specifically, the additional treatment comprises three main forms of intervention: 1) cognitive behavioral therapy for psychosis (CBTp) for patients; 2) family intervention for psychosis (FIp); and 3) case management (CM).

CBTp is based on the model developed by Kuipers *et al.*[17], Garety *et al.*[18] and Fowler *et al.*[19], and the model has already been evaluated in randomized controlled trials [20]. It is expected that an optimal number of 20–30 CBT sessions per patient will be delivered during a time frame of 9 months, with weekly sessions held during the first 3 months and fortnightly during the following 6 months. Family intervention is based on the model proposed by Leff *et al.*[21] and further developed by Kuipers *et al.*[22]. It consists of an optimal number of 10–15 sessions over 9 months with each individual family: 6 sessions in the first 3 months, and at least 1 session/month during the following 6 months. For case management, every patient/family has a dedicated case manager, who coordinates all planned interventions.

Experimental interventions are expected to begin as soon as the patient is stabilized (clinical stabilization is defined as a condition allowing the patient to collaborate in at least a brief clinical examination) and after he/she has been assessed with the ‘core’ set of baseline measures (see ‘Baseline assessment’ below). Before the start of the trial, professionals using the experimental interventions received specific training programs in CBTp (conducted as part of the scientific aims of the GET UP PIANO Project), FIp, and CM (conducted as part of the scientific aims of the GET UP TRUMPET Project). At the end of the training, an assessment of the competence achieved was performed, and detailed intervention manuals based on international standards were developed and given to the professionals as a standard to be followed for the treatment. Professionals are supported in their clinical work by a team of expert psychotherapists assigned to each CMHC. Moreover, experimental interventions provided to all patients/relatives are supervised by a team of external experts who hold one-day meetings every 2 months and are regularly available for consultation.

Fidelity will be measured at the end of the trial by an independent team by using audiotape recordings of therapy sessions, and therapists ratings of their own session. The Cognitive Therapy Scale-Revised (CTRS) [23] and the Cognitive Therapy for Psychosis Adherence Scale (CTPAS) [24] will be used, together with *ad hoc* checklists based on the specific trial intervention manuals, in accordance with the method described in Mc Hugo *et al.*[25].

#### ***Treatment as usual***

TAU is also provided by routine public CMHCs operating within the Italian National Health Service, as above. Standard care for patients with FEP typically consists of personalized outpatient psychopharmacological treatment, combined with non-specific supportive clinical management at the CMHC level. Family interventions generally consist of non-specific informal support/educational sessions. Specialized individual psychotherapeutic interventions (including CBT) for patients and specialized psychoeducational or cognitive-oriented family interventions are usually not provided because of the lack of trained professionals [26,27].

### **Enrollment procedure for community mental health centers**

The GET UP PIANO trial catchment area covers 126 CMHCs (9,951,306 inhabitants), all of which were officially asked to participate in GET UP; 117 agreed to participate, covering a catchment area of 9,304,093 inhabitants. In an effort to improve the efficiency of the study design, CMHCs were stratified before randomization, based on three variables: affiliation to the same DMH, CMHC catchment area size, and type of area (urban/mixed versus rural). Socioeconomic levels in the trial catchment area were not considered as stratification variables as they were found to be reasonably homogeneous. With the exception of staff members in five of the CMHCs (covering a catchment area of 503,000 inhabitants) the mental health staff of the remaining 112 CMHCs had received no previous training in the intervention. These first 5 centers were therefore ‘forced’ into the intervention arm and used as the expected ‘gold standard’ in the analysis, in order to measure the competence of the remaining professionals. Thus, 112 CMHCs (8,801,093 inhabitants) were available for the randomization procedure. Because of organizational needs, 32 small CMHCs were paired, based on their affiliation to the same community psychiatric service, thus resulting in 16 randomization units. Hence, in total, 96 units entered the randomization procedure.

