### **Sample size and power calculations**

For power calculations, we consider rates of relapses and/or severe psychotic symptoms to be the primary outcome measures. For a conventional trial with randomization of individual patients [51], a total of approximately 250 patients will detect a difference in terms of rates at 9 months from 25% in the TAU arm to 10% in the experimental treatment arm, with a power of 80% (two-sided test at 5%, http://statpages.org/proppowr.html). This difference could represent a plausible and realistic intervention effect [7,52,53]. The cluster randomization used for the GET UP PIANO trial purposes might result in reduced efficiency and loss of power because the within-cluster responses tend to be more similar than those of individuals from different clusters (commonalities in selection, exposure, shared environment, mutual interaction). A larger sample size will therefore be needed to compensate for this clustering effect. The clustering effect is measured as 1 + (*m*−1)*ρ*, where *m* is the number of participants per cluster (assuming equal sizes for clusters) and *ρ* the intra-cluster correlation coefficient (ICC). This clustering effect is used as an inflation factor to increase the sample size calculated, as required by an individual randomization trial [51,54]. Our approach is simplified because it does not take into account variations in the number of participants in each cluster and assumes *m* to be the average number of participants per cluster. Although this type of imbalance in cluster size may reduce the power of the trial, the loss is negligible for studies with more than 100 patients per arm [55]. Based on the additional assumptions of an ICC of 0.05 and an average of four eligible and consenting patients in each cluster, the number of patients required would be approximately 350. With a loss to follow-up of approximately 10%, we expect that a sample size of about 400 patients will yield sufficient power. Assuming an expected incidence rate in Italy for non-affective psychoses of 11 per 100,000 per year [56] and a rate for affective psychoses rate of 6 per 100,000 per year [57], a reasonable estimate of the number of patients expected over 1 year from the 116 participating CMCHs (total population 9,203,093; at-risk population about 50%) is about 800. Assuming an attrition rate of approximately 50%, due to a number of reasons, both at the cluster level (drop-out of CMHCs from the study, lack of cooperation) and at the individual level (participants who do not seek help, do not attend the public services, refuse to be involved in the study), the number of patients available for the trial would be about 400.

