### **Types of analysis**

All study data are entered into an electronic database and stored at the World Health Organization Collaborative Center for Research and Training in Mental Health and Service Evaluation of the University of Verona. The trial data manager is not involved in determining patient eligibility, administering treatment, or determining outcomes. A set of electronic and manual edit checks ensures data correctness and consistency. In accordance with the Declaration of Helsinki, patient confidentiality is fully preserved during all the study phases via anonymous data recording. Patients are assigned an identification number, both in the baseline and follow-up forms, and in the database. Anonymized data will be transferred to the trial statistician for the analyses.

Data will be analyzed when information is available for all participants. The pattern of missing values will be explored, and interactions between treatment group and completers/non-completers will be examined.

Statistical analysis will be based on an intention-to-treat (ITT) basis, comparing outcomes from all patients within CMHCs allocated to experimental treatment with those allocated to TAU. The emphasis will be on differences between these groups in terms of changes from the pre-intervention to the post-intervention phases, by taking appropriate account of the clustering. The ITT principle will allow for potential biases arising from loss to follow-up, under the assumption that missing outcomes were missing at random (MAR) using the terminology of Little and Rubin [62].

Owing to the characteristics of the cluster randomization study design, the statistical analysis cannot be masked, that is, the trial statistician will not be blinded to the treatment groups, although he/she will not be involved in determining patient eligibility, in administering treatment, in measuring outcomes, or in entering data. All analyses will be performed using Stata software (11.0 for Windows; Stata Corp.).

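### Five previously trained, non-randomised centres sit in the intervention arm and in the expected sample, and the intention-to-treat rule does not say that they stay out of the between-arm comparison

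*Protocol article*

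**What the plan says.** All of this is in the protocol article.

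- **Enrollment procedure for community mental health centers.** Of the centres approached, "117 agreed to participate, covering a catchment area of 9,304,093 inhabitants". Five of these had staff already trained in the intervention: "With the exception of staff members in five of the CMHCs (covering a catchment area of 503,000 inhabitants". On their role: "These first 5 centers were therefore ‘forced’ into the intervention arm and used as the expected ‘gold standard’ in the analysis", and the sentence ends with the purpose, "in order to measure the competence of the remaining professionals". The rest went forward: "Thus, 112 CMHCs (8,801,093 inhabitants) were available for the randomization procedure". After small centres were paired, "Hence, in total, 96 units entered the randomization procedure".
- **Randomization procedure.** The 96 units were assigned 1:1. One CMHC refused to start after randomisation.
- **Sample size and power calculations.** The recruitment forecast is "the number of patients expected over 1 year from the 116 participating CMCHs", with a total population of 9,203,093. It leads to about 800 cases and, after 50% attrition, about 400 patients.
- **Types of analysis.** The intention-to-treat analysis is defined as "comparing outcomes from all patients within CMHCs allocated to experimental treatment with those allocated to TAU".

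The sections Types of analysis, Statistical analysis and Planned subgroup analyses contain no sentence that removes, separates or adjusts for the five centres.

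**The concern.** The five centres could never have been assigned to usual care. Their place in the intervention arm was settled by prior training. The section Treatment as usual says that lack of trained professionals is why such therapies are usually not offered, so by the protocol's own account these centres differ from the norm. In them, staff experience and anything that goes with it cannot be separated from the intervention.

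If their patients enter the main comparison, they enter one arm only. A larger sample would not remove a resulting bias. Nor would the planned random-effects models, which deal with clustering and measured covariates but not with non-random assignment. The baseline comparison meant to check the randomisation would also include centres that were not randomised.

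The wording leaves two analysis sets open, and Types of analysis says that the statistician will not be blinded. The choice should therefore be fixed in the text before the data are seen.

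**Working it through.** **Inputs** (all from the protocol article): 117 CMHCs agreed, with 9,304,093 inhabitants. Five were placed without randomisation, with 503,000 inhabitants. 112 CMHCs were available for randomisation, with 8,801,093 inhabitants. The forecast rests on 116 CMHCs, 9,203,093 inhabitants, 50% at risk, incidence 11 + 6 = 17 per 100,000 per year, and 50% attrition. Loss to follow-up is 10%, the intra-cluster correlation 0.05, and the cluster size 4. The planned rates are 25% and 10%, two-sided 5%. The required number is about 350.

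**1. Are the five centres inside the forecast?**
- 117 − 5 = 112 and 9,304,093 − 503,000 = 8,801,093, as stated.
- 117 − 1 = 116 and 9,304,093 − 9,203,093 = 101,000, which fits the one refusing centre.
- So 9,203,093 = 8,801,093 + 503,000 − 101,000. The five centres are included.

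**2. The plan's own figure**
- 9,203,093 × 0.5 × 17/100,000 = 782 (stated: about 800).
- 782 × 0.5 = 391 (stated: about 400).

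The forecast reproduces to within rounding with the five centres included.

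**3. Randomised centres only** (taking the refusing centre as one of the 112, since it refused after randomisation)
- 116 − 5 = 111 centres; 9,203,093 − 503,000 = 8,700,093 inhabitants.
- 8,700,093 × 0.5 × 17/100,000 = 740 cases; × 0.5 = 370 patients.
- After 10% loss: 370 × 0.9 = 333, against the stated requirement of about 350.
- Contribution of the five centres: 503,000 × 0.5 × 17/100,000 × 0.5 = 21.4 patients, or 21.9 if the rounded 400 is scaled by 503,000/9,203,093 = 5.5%.
- Relatives, whose forecast starts from the same patients and assumes 20% unavailable: 370 × 0.8 = 296, against 400 × 0.8 = 320.

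**4. Share of the experimental arm if pooled** (assumption: the randomised population splits evenly)
- 8,801,093/2 = 4,400,547 per arm; adding 503,000 gives 4,903,547.
- 503,000/4,903,547 = 10.3%. If the refusing centre came from the experimental arm, the share is 10.5%.
- In clusters: 48 + 5 = 53 against 48.

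**5. Possible shift in the experimental-arm rate.** The documents give no outcome data for these centres. If their relapse rate differed by 5, 10 or 15 points for reasons other than the intervention (an assumed range), the arm rate would move by 0.103 × 5 = 0.5, 0.103 × 10 = 1.0 or 0.103 × 15 = 1.5 points. The planned difference is 15 points.

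**6. Power without the five centres**
- Design effect: 1 + (4 − 1) × 0.05 = 1.15.
- Effective number: 333/1.15 = 290, or 145 per arm.
- Power for 25% versus 10%: 92% by the normal approximation, 90% with continuity correction.
- With 391 recruited (352 after loss, effective 306), the same calculation gives 94% and 91%.

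This recomputes power from the stated rates and does not start from the protocol's totals. Those totals are more conservative: 350/250 implies an inflation of 1.4. With 1.4, power at 370 recruited is 87% (82% with continuity correction), still above 80%.

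**The case against.** The strongest reply is that the article never says the five centres are pooled. The section Randomization procedure uses allocation language for the 96 randomised units, while the five are described as forced in. So *allocated* in the intention-to-treat rule may well mean randomised. The benchmark purpose, "in order to measure the competence of the remaining professionals", points the same way, and it is the role that they should have. The 116-centre figure is a recruitment forecast and does not define an analysis set. Finally, this is a condensed article, and analysis sets are commonly spelled out in a fuller protocol or analysis plan.

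Much of this stands. The text is ambiguous; it is not an instruction to pool. A reader might infer that the main comparison as specified mixes randomised and hand-picked clusters and so loses the protection of randomisation. The documents do not support that. They give one disclosed criterion, prior training, and even under pooling about 90% of the experimental arm and all of the control arm would be randomised. A reader might also infer that the bias favours the intervention. The term *gold standard* makes that plausible, but there are no outcome, service-quality or case-mix data on these centres.

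The reply does not remove the point. The same sentence puts the centres in the intervention arm and in the analysis, the sample size section counts their patients, and the intention-to-treat rule has no exception. The article has itself stated arm membership, analysis rule and expected number, and together they permit non-randomised clusters in one arm. That is more than a detail left to another document.

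**Conclusion.** The point holds as a defect of specification. Following the text can put five non-randomised, previously trained centres into the experimental arm of the main comparison. Under an even split of the randomised population they would be about 10% of that arm. The size and direction of any bias are unknown; the 0.5–1.5 point shift is illustrative only and rests on an assumed difference.

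The expected 400 also overstates the randomised sample. The protocol's inputs give about 370 from randomised centres, taking the refusing centre to be one of those randomised. The 333 left after loss is slightly below the stated requirement of about 350, but the recomputed power of about 90–92% shows that restricting the comparison does not endanger the trial's planned power.

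**What to change.** 1. In Types of analysis, state that every between-arm efficacy comparison, for patients and for relatives, uses only the 96 randomised units, analysed as randomised, and say how the unit containing the refusing centre is handled.
2. State that the five non-randomised centres serve as the competence benchmark. If a comparison including them is wanted, label it as a sensitivity analysis.
3. In Sample size and power calculations, restate the expected randomised sample as about 370 recruited and about 333 after 10% loss. Acknowledge that this is slightly under the stated 350, and give the recomputed power with its assumptions. Restate the forecast for relatives on the same basis.

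The cost is a few sentences and about 21–22 patients leaving the primary comparison. No data collection changes.
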